# TRANS-FOODS study protocol: an observer-blinded, randomized controlled study to assess transcutaneous sensitization to peanut protein in adults with and without atopic dermatitis

**DOI:** 10.1093/skinhd/vzag046

**Published:** 2026-06-25

## Abstract

**Background:**

The rising prevalence of allergic conditions like atopic dermatitis (AD) and food allergies is complex. The dual allergen exposure hypothesis suggests that allergen exposure through skin, particularly in those with AD, can lead to sensitization. This may be exacerbated by skin massage which can enhance allergen absorption by opening the cutaneous appendages. The TRANS-FOODS project aims to elucidate the mechanisms underlying transcutaneous peanut allergy sensitization and evaluate novel preventative strategies, including alterations in peanut processing and adapting skincare practices. As part of the project, a randomized controlled study at King’s College London has been set up to investigate whether skin massage facilitates transcutaneous uptake of peanut allergens, particularly in individuals with AD, and whether a barrier-enhancing cream can mitigate this effect.

**Methods:**

We report the study protocol for a single-site, observer blind randomized controlled trial, where healthy adults and adults with AD (*n* = 130) will be recruited and randomized, applying a peanut protein–containing extract to their outer forearm twice daily with/without massage and with/without a barrier-enhancing cream for a total of 4 weeks. The primary outcome is the potential detection of inflammatory cytokines in skin interstitial fluid (ISF), using a novel non-invasive ISF suction device. In addition, we will study whether the intervention enables detection of peanut protein components in retrieved skin ISF and results in increased transepidermal water-loss measurements.

**Discussion:**

To the best of our knowledge, this study will be the first to use a skin massage intervention with a peanut protein–containing solution and a novel ISF extraction device to understand the effects of massage on the immune system and explore the biological signals associated with food sensitization.

**Protocol registration:**

The trials are registered on ISRCTN (ISRCTN12492694) and ClinicalTrials.gov (NCT05407012).

Allergic conditions, such as atopic dermatitis (AD) and food allergies, have become increasingly common, particularly in developed nations. In the UK, AD affects around 20% of children, while nut allergies impact over 2% of the paediatric population.^1^

The development of a food allergy is a complex process, with various hypotheses suggesting an interplay between genetics, diet, skin exposure and the gut microbiome.^2^ One of the most researched ideas is the dual allergen exposure hypothesis, which suggests that early exposure to allergens via the skin may lead to sensitization, particularly in individuals with AD, while oral food protein introduction conveys tolerance.^3–5^ A study by Brough *et al*. demonstrated that infants exposed to peanut protein in household dust were at increased risk of developing peanut allergies, especially if they had *FLG* mutations.^6^ There is also growing evidence that skin massage may exacerbate transcutaneous sensitization to allergens.^7^ Animal studies have shown that mice sensitized to peanut via skin exposure experienced anaphylaxis when later exposed through ingestion, but only when the skin barrier was compromised.^8^

Data from the Barrier Enhancement for Eczema Prevention (BEEP) trial^9^ and the Enquiring About Tolerance (EAT) study^10^ suggest that daily moisturizer application may enhance allergen exposure, potentially through contamination with food proteins. Additionally, an earlier UK cohort study of nearly 14,000 children found that applying creams containing peanut oil to the skin of infants with AD significantly increased the risk of developing peanut allergies.^11,12^

One potential approach to mitigate this risk is early-life dietary exposure to food proteins, which may induce tolerance to these proteins. However, as shown in the EAT study, where only 42% of participants were able to adhere to regular feeding of allergenic foods, ensuring consistent ingestion of allergens in infants is challenging.^7^ Therefore, strategies to reduce skin exposure to food proteins are an important additional food allergy prevention measure. However, the design of such interventions is complicated due to our limited understanding of how peanut allergens make contact with the cutaneous immune system, triggering allergic sensitization.

The European Union Horizon 2020-funded TRANS-FOODS project aims to understand the exact mechanisms behind transcutaneous sensitization and to develop and test novel prevention approaches. Here we present the protocol for an intervention study that forms part of the TRANS-FOODS programme of work to examine the immune responses to peanut allergens in individuals with and without AD, with and without skin massage. Specifically, we aim to determine whether peanut allergen components can penetrate the skin through regular massage and whether this effect is amplified in individuals with a compromised skin barrier. We will also investigate whether preapplication of a barrier-enhancing cream can reduce transcutaneous uptake of peanut proteins.

The primary objective of this study is to determine whether inflammatory cytokines, such as interleukin (IL)-4 and IL-13 can be detected in skin interstitial fluid (ISF) after regular massage using a peanut protein-containing extract.

The secondary objectives are:

To clarify whether this effect is amplified in those with an ­impaired skin barrier (patients with AD vs. healthy control ­p­articipants).To test whether peanut protein components present in skin ISF are able to induce activation of basophils in blood of ­donors allergic to peanuts.To assess whether the transcutaneous uptake of peanut protein can be reduced by the prior use of a barrier-enhancing cream.

## Patients and methods

This study protocol was designed following the SPIRIT (Standard Protocol Items: Recommendations for Interventional Trials) guidelines.^13^

### Study design

This is a single-site, observer-blinded, randomized controlled study.

### Eligibility criteria

#### Inclusion criteria

Healthy adults and adults with AD (fulfilling the refined Hanifin and Rajka criteria) between the age of 18 and 65 years who can provide written informed consent and have competent use of the English language will be eligible to take part. Individuals must also be willing to comply with all study requirements.

#### Exclusion criteria

Adults with a history of peanut allergy or a positive skin prick test (SPT) to peanut (SPT >0 mm wheal size) at baseline will not be eligible to participate in the study. No regular consumption of peanut products, widespread AD (particularly if this involves the test sites of the forearms) and the inability to provide informed consent will also lead to exclusion.

### Intervention

A total of 60 healthy adult volunteers and 60 adults with AD will be recruited and then randomized to ensure an even split between groups. A peanut protein extract will be used in all participants. The two groups will then be evenly split into the following groups through computer-generated randomization:

Group 1: application of the barrier-enhancing cream 30 min before application of the peanut protein extract ± massage after extract application.

Group 2: no application of the barrier-enhancing cream, just application of the peanut protein extract ± massage after extract application.

This will generate 8 intervention groups, each comprising 15 participants (outlined in Figure 1). Participants will wash their hands and forearms with soap and water before applying the test interventions to the central area of the nondominant outer forearm twice daily with a 5-min massage throughout the 4-week study period. The control formulation (with no protein extract) will be applied without massage to the central, dominant outer arm twice daily as the control. Clear instructions on the massaging technique will be given to all participants, which they will then follow at home using video guidance. Standardized instructions, demonstration videos and written guidance will be used to promote consistent technique and frequency across participants, with weekly text reminders to reinforce adherence and reduce interparticipant variability. Adherence will be monitored using daily record surveys.

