### Statistical methods

Comparison of baseline demographic characteristics of study participants across all eight intervention groups will be done using descriptive methods. Adherence to the intervention, including the reasoning behind noncompliance, withdrawal from the study and loss to follow-up, will be summarized. Any adverse events reported by study participants through the daily record surveys or within the visits will also be summarized.

Descriptive and inferential methods will be used for the main analysis. The primary analysis will comprise analysis of covariance to estimate the difference in concentration of inflammatory cytokines in skin ISF between massaging and no massaging patients as per the primary objective by intention-to-treat at week 4. The terms in the model will include the effects of having impaired skin, use of barrier-enhancing cream and massage. Covariates such as gender, ethnicity, baseline TEWL and baseline values of the outcome will be included, with TEWL considered a key mediating factor. Secondary outcomes, including the effect of impaired skin, use of barrier-enhancing cream, and basophil and mast cell activation, and peanut-specific IgE levels, will be analysed similarly. Interaction effects, including those involving massage frequency (categorical and continuous), will also be tested, with significance levels set at 5% for main effects and 10% for interactions. Analyses will account for non-normal data using transformations or nonparametric tests like the Wilcoxon–Mann–Whitney test.

The proportion of participants lost to follow-up after randomization will be summarized in each intervention group. This ­summary will include reasons for loss to follow-up including ­participant withdrawal, withdrawal by the clinical study team and other specified reasons. Baseline characteristics of those missing a week 4 assessment for healthy vs. skin impaired volunteers, cream application vs. no barrier-enhancing cream and massaging vs. no massaging will be compared descriptively to those with complete follow-up at week 4. There will be no imputation for missing data.

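### The Intervention section contradicts its own massage allocation: its conduct text extends the massage to all participants, with no exception for the no-massage groups

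*Protocol article*

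**What the plan says.** The protocol article makes massage a randomised factor in several places:

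- Intervention, cream group: "application of the barrier-enhancing cream 30 min before application of the peanut protein extract ± massage after extract application".
- Intervention, no-cream group: "no application of the barrier-enhancing cream, just application of the peanut protein extract ± massage after extract application".
- Intervention, result of the split: "This will generate 8 intervention groups, each comprising 15 participants".
- Abstract, Methods: "twice daily with/without massage and with/without a barrier-enhancing cream for a total of 4 weeks".
- The aims at the end of the introduction also describe study conditions with and without massage.
- Statistical methods: the primary analysis of covariance, by intention-to-treat at week 4, is "to estimate the difference in concentration of inflammatory cytokines in skin ISF between massaging and no massaging patients".

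The conduct text that follows the allocation in the Intervention section drops the distinction. Participants, not further specified, are described as "applying the test interventions to the central area of the nondominant outer forearm twice daily with a 5-min massage throughout the 4-week study period". Then: "Clear instructions on the massaging technique will be given to all participants, which they will then follow at home using video guidance". Videos, written guidance and weekly texts are to keep technique and frequency consistent across participants. The only application that this text expressly exempts from massage is the control formulation on the dominant arm.

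**The concern.** The allocation and the conduct text cannot both be followed. If four of the eight groups receive extract without massage, then it is not true that all participants follow massage instructions at home, or that the test intervention is applied with a 5-minute massage without qualification. The paragraph excludes massage explicitly for the control arm, so its silence about the no-massage groups on the test forearm is conspicuous.

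Massage is the factor behind the primary contrast, and participants carry it out themselves at home for 4 weeks. What each group is told is therefore a main means of keeping the arms distinct. A participant allocated to no massage who massages anyway still counts as no massage under intention-to-treat, which pulls the estimated effect towards zero. A small or null effect would then be hard to interpret, because it could reflect no effect of massage or poor separation of the arms.

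**Working it through.** **1. The passages side by side**

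| Element | Allocation and analysis text | Conduct text |
|---|---|---|
| Who massages the test forearm | Half of each population | Participants, unqualified |
| Who receives and follows massage instructions | Not stated by group | All participants |
| What the no-massage groups do on the test forearm | Extract without massage | Not stated |

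Nothing in the article reconciles the two columns.

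**2. The plan's own power figure**

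Inputs from Sample size: coefficient of variation (CV) about 20% for cytokines, 15 per group, a doubling, over 90% power. Two-sided 5% is assumed, since the article gives 5% for main effects without sidedness.

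- Log-scale SD = √ln(1 + 0.20²) = 0.198, and the effect = ln 2 = 0.693.
- SE = 0.198 × √(2/15) = 0.072, and 0.693/0.072 is about 9.6, far above 1.96.
- Power exceeds 99.9%, so the stated figure is reproduced.

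**3. Illustration of attenuation**

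Let c be the share of no-massage participants who massage. The article gives no value, so c is varied from 0 to 100%. Assumptions: full adherence in the massage groups, the full effect in those who cross over, normal approximation, no covariate adjustment.

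- Apparent ratio = 2^(1−c).
- Log effect = (1−c) × ln 2.
- The variance of the no-massage arm rises by c(1−c)(ln 2)².
- Massage against no massage overall: 4 groups × 15 = 60 per side.

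| c | Apparent ratio (true 2.00) | Power, 60 vs 60 | Power, 15 vs 15 |
|---|---|---|---|
| 0 | 2.00 | >99.9% | >99.9% |
| 25% | 1.68 | >99.9% | 99.8% |
| 50% | 1.41 | >99.9% | 85% |
| 75% | 1.19 | 90% | 37% |
| 100% | 1.00 | 2.5% | 2.5% |

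The last row is the upper-tail rejection rate when no contrast is left. Example for c = 50% at 60 vs 60: effect 0.347; SE = √[(0.0392 + 0.0392 + 0.25 × 0.480)/60] = 0.058; 0.347/0.058 is about 6.0.

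**4. Dependence on the CV**

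The power column rests on the plan's CV. At 60 vs 60 and c = 50%, power is 99.9% at CV 30%, 95% at CV 50% and 59% at CV 100%. The apparent ratio does not depend on the CV.

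**The case against.** The strongest reply is that the design is clear and only the wording slipped. The abstract, the introduction, the allocation text and the statistical methods all show that no-massage groups are intended, and no sentence tells a participant allocated to no massage to massage. The 5-minute massage most naturally describes the massage condition, with a qualifier omitted. The article also condenses a full protocol; that document and the participant materials are not shown, and they may hold separate instructions. This largely stands as an account of intent. It does not remove the contradiction, which lies in what the article states and not in what it leaves out.

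Three stronger readings are tempting, and the documents support none of them.

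- A reader might infer that crossover is built into the plan. Taken fully literally, the text would abolish the no-massage groups that the same section has just created, which points to a drafting conflict and not to planned crossover.
- A reader might infer that nothing else keeps the arms apart. In fact the clinical team knows each allocation (Masking), daily surveys monitor compliance (Participant recruitment, data collection methods and timeline), and Statistical methods summarises adherence and tests interactions with massage frequency, which implies that frequency is recorded. The article does not say that it is recorded in the no-massage groups.
- A reader might infer a serious loss of power. On the plan's own CV of 20% and a true doubling, the 60 vs 60 contrast keeps over 99.9% power even at 50% crossover. That answers the power question only, since the estimate would still be biased towards zero.

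**Conclusion.** The point holds as an internal contradiction about the randomised factor behind the primary analysis. It does not show that the contrast is in fact diluted. If the conduct text were followed as written, the no-massage groups would be taught the massage and might perform it. The intention-to-treat effect would then shrink in proportion to the share who did, reaching zero if all did. The size cannot be established, because that share is nowhere given; the figures above are illustrations over an assumed range. The risk is to the estimate and its interpretation more than to power under the plan's stated assumptions. Correction is warranted because the text concerns the primary contrast and is easily put right.

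**What to change.** Reconcile the Intervention section with its own allocation:

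- State that the 5-minute massage, the massage instructions and the massage video apply only to the groups allocated to massage.
- State what the no-massage groups are told for the test forearm.
- If the full protocol or participant materials already make this distinction, carry it into the article's text.
- Use the existing daily REDCap survey to record, in every arm, whether the test site was massaged, and report crossover by arm alongside the planned adherence summary.

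The cost is protocol wording, participant materials for the no-massage groups where these do not yet exist, and one survey item. No additional participants, visits or procedures are needed.

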**Figure 1 vzag046-F1:**
[figure not shown]
Study flowchart: the peanut extract will be applied to the nondominant outer forearms of each participant, while the peanut extract vehicle will be applied as a control to the dominant forearm. Half of the participants will also have a barrier-enhancing cream applied to the nondominant forearm, 30 min prior to applying the peanut extract. Clinical and sample assessments will be taken at baseline and at week 4. AD, atopic dermatitis; IL, interleukin; TSLP, thymic stromal lymphopoeitin.

Samples of skin ISF will be collected from the control and intervention application sites. Transepidermal water-loss (TEWL) measurements will be taken from the inner forearm. SPT to peanut extract will be performed at baseline to ensure participants are not allergic to peanuts. All baseline measures will be repeated after the 4-week intervention period (Figure 1). Details of the study procedures are outlined below.

### Study procedures and analysis

#### Skin interstitital fluid sampling

Before the study, the potassium phosphate buffer and devices will be autoclaved. Each participant will have their own allocated device. Before use for a different participant, the chambers will be autoclaved. This study will be conducted under standardized conditions. Before commencing the study, participants will be given time to adapt to room conditions and the same investigator will perform all measurements. The skin will be wiped and cleaned using 70% ethanol and tissue. For each participant, the designated skin area will be marked with a washable marker pen. Two tapes will be applied and removed sequentially to remove any skin debris or protein. The skin will again be wiped and cleaned using 70% ethanol and tissue. A 150-µL aliquot of 0.1 M potassium phosphate buffer (sterile, pH 7.4) will be added to the chamber and –9.0 PSI (gauge reading) will be applied for 10 min. After this, pressure will be removed, the buffer will be collected by pipetting up and down and transferred into a 1.5-mL sample-collection tube. During the entire process, the area under the chamber will be carefully monitored for any signs of redness, and the procedure will be stopped if any pain or dark redness is observed. This will be repeated a second time on the arm where the intervention will be applied or has been applied, to ensure two samples of ISF are collected. The same procedure will be done once on the control arm. All samples will be stored on dry ice and then transferred to storage at −80°C until analysis.

#### Transepidermal water loss measurement

TEWL will be measured using a noninvasive commercial measuring device, the Biox Aquaflux AF200 condensing chamber probe (Biox Systems, London, UK). The measurement will be achieved by placing the TEWL probe on the surface of the skin on the inner forearm for 1 min. Measurement will be conducted in triplicate, with the mean taken as the true value.

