#### Skin prick testing

Before testing, we will confirm that participants have not taken short-acting antihistamines within the past 48 h or long-acting antihistamines within the past 7 days. All SPTs will be conducted using Allergopharma and Lofarma extracts (available from Diagenics, Milton Keynes, UK), along with positive (histamine 0.1%) and negative control (50% glycerol, 50% buffered saline) solutions. Tests will be performed on the inside of the forearm on eczema-free areas (for participants with AD). A small drop of the control solutions and each allergen solution will be applied to the skin, and the surface will be pricked through each drop using a sterile, single-use lancet (Allegropharma, available from Diagenics). Skin test sites will be measured after 15 min. The wheal and flare will be measured after 15 min by recording their widest diameters and its perpendicular measurement, and the mean measurement will be recorded.

If the negative control produces a wheal ≥3 mm, we will reschedule the test after 7 days. If the positive histamine control produces a wheal ≤3 mm, then the test will be repeated immediately. Should the repeat result remain ≤3 mm, the test will also be rescheduled after 7 days.

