### Endpoints

The primary endpoint will be the change from baseline in inflammatory cytokine concentrations (interferon-γ, IL-10, IL-12p70, IL-17, IL-1β, IL-2, IL-4, IL-6 and tumour necrosis factor-α) in skin ISF following regular massage with a peanut protein-containing extract.

The secondary endpoints will be the potential detection of peanut protein components in retrieved skin ISF. If detected, we will also measure whether the retrieved peanut protein can activate mast cells and basophils, comparing the study arms. Raised TEWL will also be a secondary endpoint.

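### TEWL is read on the inner forearm while the interventions go on the outer forearm, so the secondary endpoint of raised TEWL is poorly placed to detect a local effect of massage or cream

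*Protocol article*

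**What the plan says.** **Where TEWL is measured.** The Transepidermal water loss measurement section specifies "placing the TEWL probe on the surface of the skin on the inner forearm for 1 min", in triplicate. The text after Figure 1 agrees: "Transepidermal water-loss (TEWL) measurements will be taken from the inner forearm". Neither place says which arm.

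**Where the products go.** The Intervention section has participants "applying the test interventions to the central area of the nondominant outer forearm twice daily". The Figure 1 caption repeats the site for the extract: "the peanut extract will be applied to the nondominant outer forearms of each participant". The control formulation "will be applied without massage to the central, dominant outer arm twice daily as the control". The caption puts the cream on the nondominant forearm without adding that this is the outer side. The Intervention section supplies that, because the cream is part of the test intervention.

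**Where interstitial fluid (ISF) is taken.** The text after Figure 1 places ISF sampling at the intervention and control application sites.

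**What TEWL is for.** The Endpoints section states: "Raised TEWL will also be a secondary endpoint". The abstract (Methods) presents a rise in TEWL as something the intervention may cause. The Statistical methods section lists baseline TEWL as a covariate and, in the same sentence, describes TEWL as an important mediator.

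**The concern.** Massage, extract and cream are local exposures, given to a defined area of outer-forearm skin. An endpoint meant to show whether they disturb or protect the barrier should be read on that skin. As written, the probe goes on the other side of the forearm.

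The stake is misinterpretation. A flat TEWL result could be reported as massage leaving the barrier intact, or as the cream having no barrier effect, when the treated skin was never measured. Both questions are close to the trial's stated aims. Analysis cannot repair the problem afterwards, because the readings from treated skin would not exist.

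**Working it through.** **1. Sites side by side**

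| Item | Site | Where stated |
|---|---|---|
| Extract, massage | Nondominant outer forearm, central | Intervention; Figure 1 caption (extract) |
| Cream | Nondominant forearm; outer by the Intervention section | Figure 1 caption; Intervention |
| Control formulation | Dominant outer arm, central | Intervention |
| ISF samples | Application sites, both arms | Text after Figure 1 |
| TEWL | Inner forearm, arm not stated | Text after Figure 1; TEWL section |

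The TEWL site is given twice and consistently, and so is the outer-forearm site for the extract. This does not look like a single slip. The sentence directly before the TEWL sentence ties ISF sampling to the application sites, so the article makes that link where it intends it. It describes no TEWL reading on treated or vehicle-treated skin.

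**2. The plan's own figures**

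The Sample size section gives coefficients of variation of about 20% (ISF cytokines), 8% (peanut protein) and 30% (basophil and mast cell tests), with 15 per group. It gives nothing for TEWL, so there is no TEWL figure to reproduce.

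**3. Illustration of the loss**

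Inputs from the article:
- Eight groups of 15, half of them with massage, so 4 × 15 = 60 against 60.
- Significance level 5% for main effects.

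Assumptions not in the article:
- Two-sided test, normal approximation, no covariate adjustment.
- Treated-site effect d of 0.5, 0.8 or 1.0 SD.
- A fraction f of that effect present at the measured site.

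Formula: with z = d·f / √(2/60) and √(2/60) = 0.1826, power = Φ(z − 1.96) + Φ(−z − 1.96).

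Worked case, d = 0.5:
- f = 1: z = 0.5/0.1826 = 2.74, power = Φ(0.78) = 0.78.
- f = 0.25: z = 0.125/0.1826 = 0.68, power = Φ(−1.28) + Φ(−2.64) = 0.11 after rounding.
- f = 0: z = 0, power = 2·Φ(−1.96) = 0.05.

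| d (SD) | f = 1 | f = 0.5 | f = 0.25 | f = 0 |
|---|---|---|---|---|
| 0.5 | 0.78 | 0.28 | 0.11 | 0.05 |
| 0.8 | 0.99 | 0.59 | 0.20 | 0.05 |
| 1.0 | >0.99 | 0.78 | 0.28 | 0.05 |

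The last column is the purely local case: rejection happens only at the significance level, whatever the true effect on treated skin.

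**The case against.** The site mismatch itself is hard to dispute. The fair objections concern how far it reaches, and most of them stand.

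- **A reader might infer that the TEWL endpoint cannot show any effect and has exactly 5% power.** That requires zero effect on the inner forearm, which the article does not establish. It does not give the size of the treated area, and some spill-over is not excluded. The article gives no reason to expect spill-over, but the supportable statement is that the site is poorly placed for a local effect.
- **A reader might infer that every TEWL comparison is lost.** It is not. Atopic dermatitis against healthy skin is a comparison of general barrier status, and the inner forearm is usable for that.
- **A reader might infer that a planned mediation analysis uses the wrong skin.** The mediator phrase stands beside baseline TEWL in the covariate list, and no model with week-4 TEWL as mediator is specified. It may only mean that general barrier function influences uptake. The site would matter if week-4 TEWL were used to mediate a local effect.
- **A reader might infer that skin prick wheals disturb the reading**, since "Tests will be performed on the inside of the forearm on eczema-free areas". The article does not say that the two procedures share an arm or a spot, or which comes first. A condensed article can leave visit order to the full protocol, so this does not support the point.
- **The primary endpoint does not depend on this.** Cytokines are measured in ISF from the application sites, and so are peanut protein and the cell-activation tests.

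It could also be said that a condensed article leaves site details to the full protocol. That does not answer the point: the article does fix a site, and the site does not fit the endpoint it names.

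**Conclusion.** The point holds for one secondary endpoint. Raised TEWL, treated as an outcome of the intervention, is read on skin that receives none of the interventions. It is largely insensitive to a local effect of massage or cream, and if the effect is purely local, power is close to the significance level. The power figures rest on assumed effect sizes and assumed spill-over fractions; they show the direction and rough scale of the loss and do not predict this trial's power.

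Three things stay sound: the atopic dermatitis versus healthy comparison, baseline inner-forearm TEWL as a general barrier covariate, and the ISF-based primary endpoint as an outcome. The documents do not support a wider claim that all TEWL results, the mediator statement or the primary inference fail.

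**What to change.** - At baseline and week 4, measure TEWL in triplicate at the outer-forearm application site and at the matching control site on the other arm.
- Take these readings before the ethanol cleaning, tape stripping and suction of the ISF procedure, which act on the same skin. Set a standard interval since the last product application, so that residual cream or extract does not distort the reading.
- Define the endpoint as week-4 application-site TEWL adjusted for baseline at the same site.
- Keep inner-forearm TEWL only as a baseline barrier covariate.
- If the site cannot be changed, or for participants already measured only on the inner forearm, do not use that reading as an intervention endpoint or as a mediator of a local effect, and say so in the Endpoints and Statistical methods sections.

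The cost is a change of protocol wording and a few more minutes per visit with the same device and staff. Participants already measured will lack the new reading, so the TEWL endpoint will rest on fewer people than the other outcomes.
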